### Sample size and statistical analysis of primary outcome

- A total of 40 patients will be enrolled in this pilot study
- Rationale for sample size
  - Primary safety outcome: weekly frequency of mild, moderate, or severe hypoglycemic episodes by discrete glucose meter values and/or a reference blood glucose level if the subject is seen in a hospital (emergency room)
  - Assumed mean weekly mild, moderate, or severe hypoglycemic episodes by discrete glucose values: 0.6
  - Assumed SD for weekly mild, moderate, or severe hypoglycemic episodes by discrete glucose values: 0.8
  - Assumed intra-class correlation between baseline and on-treatment weekly mild, moderate, or severe hypoglycemic episodes by discrete glucose values: 0.6
  - Estimated variance of change from baseline (a minimum of 4 weeks up to 16 weeks) to on-treatment (24 weeks) mean weekly mild, moderate, or severe hypoglycemic episodes (estimated from SD and intraclass correlation, accounting for 3:1 ratio of on-treatment to baseline period lengths): 0.41
  - Type I error: 0.05 (1-sided for equivalence)
  - Power: 0.9
  - Expected percent increase from baseline in mean weekly mild, moderate, or severe hypoglycemic episodes during the treatment period with RT-CGM while using the

- glucose pump: 0%
- Equivalence limit (maximum percent increase in mean weekly mild, moderate, or severe hypoglycemic episodes): 35% (0.6 vs. 0.81 episodes per week)
- Method for sample size calculation: One sample test for equivalence (Chow, Shao and Wang, Sample Size Calculations In Clinical Research, Taylor & Francis, NY, 2003: p. 52-53)
- Software: Centre for Clinical Trials, Chinese University of Hong Kong -- [http://www.cct.cuhk.edu.hk/stat/mean/osm\\_equivalence.htm](http://www.cct.cuhk.edu.hk/stat/mean/osm_equivalence.htm)
- Calculated sample size: N = 37

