### 8.3 Statistical issues

The goals of this pilot study are to assess the safety, feasibility, and potential for efficacy of RT-CGM as an adjunct to SMBG in conjunction with insulin pump therapy to produce improved glycemic control in a small sample of diabetic patients with gastroparesis. The findings are intended to provide the foundation

for determination of whether a large multicenter randomized, controlled efficacy trial of RT-CGMS as an adjunct to SMBG in conjunction with insulin pump therapy vs. conventional diabetes management should be conducted in diabetic patients with symptomatic gastroparesis. The current study will provide valuable pilot data to inform the design of an efficacy trial.

As noted above, the primary safety outcome measure for our study is the weekly frequency of mild, moderate and severe hypoglycemic episodes. There is very limited (published or from other sources) information on the frequency of mild, moderate and severe hypoglycemic events in tightly controlled diabetic gastroparesis. Thus, for planning purposes, we relied upon a consensus of the clinical experiences of the investigators ([name], [name], and [name]) for estimates needed for the statistical design of this pilot study:

- Assumed mean weekly mild to moderate hypoglycemic episodes by SMBG: 0.6
- Assumed SD for weekly mild to moderate hypoglycemic episodes by meter glucose: 0.8
- Assumed intra-class correlation between baseline and on-treatment weekly mild, moderate and severe hypoglycemic episodes by meter glucose: 0.6
- Estimated variance of change from baseline (a minimum of 4 weeks up to 16 weeks) to on-treatment (24 weeks) mean weekly mild, moderate and severe hypoglycemic episodes (estimated from SD and intraclass correlation, accounting for 3:1 ratio of on-treatment to baseline period).

We planned the study to test the safety hypothesis that, compared to a minimum of 4 weeks up to 16 weeks of baseline treatment, any increase in mean weekly mild, moderate and severe hypoglycemic events during approximately 24 weeks of insulin pump treatment and RT-CGM was no larger than 35%. Using a one-sample equivalence z-test and assuming one-sided Type I error of 0.05, power =0.9, expected percent increase from baseline to on-treatment=0%, and equivalence limit of 35% (0.6 vs. 0.81 episodes per week), the calculated sample size was N=37. The method of calculation and software used are as follows:

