- Method for sample size calculation: One sample test for equivalence (Chow, Shao and Wang, Sample Size Calculations In Clinical Research, Taylor & Francis, NY, 2003: p.52-53)23
- Software: Centre for Clinical Trials, Chinese University of Hong Kong24  
[http://www.cct.cuhk.edu.hk/stat/mean/osm\\_equivalence.htm](http://www.cct.cuhk.edu.hk/stat/mean/osm_equivalence.htm)

We increased the target sample size approximately 10% to N=40 patients to allow departures from assumptions. In addition, we plan to review safety data only with the DSMB when approximately N=10 patients have completed the study. The DSMB will advise on whether or not it is safe to proceed towards the full sample size of 40 patients.

An important, but secondary, efficacy outcome is reduction in hemoglobin A1c. However, if we assume that 25% (10 patients) do not achieve good glycemic control (hemoglobin A1c >7% at 12 and 24-weeks), the confidence limits on the actual proportion not achieving good control with 40 patients will be wide with a half-width of  $\pm 16\%$ . A sample size of 40 will provide adequate power to detect clinically meaningful changes in some measures of gastroparesis symptoms, quality of life, or on measures of gastric motor and sensory and autonomic function in this pilot study; however, a larger, study with a control group would be needed to provide evidence of efficacy. A 25% reduction in mean from a baseline GCSI score of  $27 \pm 15$  to  $20 \pm 15$ , with a sample size of 40, can be detected with >99% power, again assuming a Type I error of 0.05 and a modest intra-class correlation between baseline and follow-up GCSI measures. Comparisons within GLUMIT-DG subgroups will have limited statistical power; for example, we will compare Type 1 versus Type 2 diabetics for indications of differential outcomes,

however, the power for such comparisons will be low -- only 57% power for the primary hypoglycemic outcome measure with equal numbers of Type 1 or type 2 diabetics and less power if the numbers are unequal.

Questions of efficacy and subgroup comparisons for differential responses are best addressed in the context of a larger multicenter, randomized, controlled trial; however, the GLUMIT-DG pilot study will provide key information on variability in outcome measures at baseline and over time, and on the potential effect sizes - this information is not currently available for other sources and is needed to inform trial design.

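### The stated inputs give N = 101 (80 if only the upper limit is tested), not N = 37, so 40 patients do not provide 90% power to exclude a 35% increase in hypoglycemic episodes

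*Protocol*

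**What the plan says.** The design synopsis lists the planning inputs. The mean is "Assumed mean weekly mild, moderate, or severe hypoglycemic episodes by discrete glucose values: 0.6" and the spread is "Assumed SD for weekly mild, moderate, or severe hypoglycemic episodes by discrete glucose values: 0.8". The correlation between baseline and on-treatment values is 0.6. The variance of the change is derived from these, "accounting for 3:1 ratio of on-treatment to baseline period lengths): 0.41". The synopsis then reports "Calculated sample size: N = 37".

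Section 8.3 repeats the calculation, although its own bullet on the variance of change carries no figure. It names a one-sample equivalence z-test, "assuming one-sided Type I error of 0.05, power =0.9, expected percent increase from baseline to on-treatment=0" percent, with an "equivalence limit of 35% (0.6 vs. 0.81 episodes per week), the calculated sample size was N=37". The hypothesis is worded in one direction: any increase is to be no larger than 35%. The target is then raised by about 10%, to 40.

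Later in section 8.3, the comparison of Type 1 with Type 2 patients is described as having "only 57% power for the primary hypoglycemic outcome measure with equal numbers of Type 1 or type 2 diabetics". Neither the test nor the size of difference behind that figure is given.

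**The concern.** The limit is given both as a percentage (35%) and as two rates (0.6 and 0.81 per week). The two agree, and both mean an absolute difference of 0.21. The SD of the change is √0.41 = 0.64 per week, about three times that limit. Thirty-seven patients look too few to exclude so small a shift with 90% power.

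Safety is the principal objective, and this is the hypothesis that sets the sample size. If the power is well below 90%, a treatment that leaves the hypoglycemia rate unchanged would often fail to exclude a 35% increase. A reader who trusted the stated 90% could take that failure as a sign of harm. The results are also meant to inform whether a larger randomized trial should follow.

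**Working it through.** **Inputs (synopsis and section 8.3).** Mean 0.6 per week; SD 0.8; correlation 0.6; on-treatment to baseline ratio 3:1; variance of change V = 0.41; one-sided alpha 0.05; power 0.9; true change 0; limit d = 0.81 − 0.60 = 0.21.

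**1. The variance reproduces.** V = 0.64 + 0.64/3 − 2 × 0.6 × 0.8 × (0.8/√3) = 0.64 × (1 + 1/3 − 1.2/√3) = 0.4099. So 0.41 is a variance in (episodes/week)², not an SD.

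**2. Sample size from the stated inputs.**
- Equivalence: n = (z₀.₉₅ + z₁₋β/₂)² V/d². With β = 0.10 both z values are 1.645, so n = 10.82 × 0.41/0.0441 = 100.6, giving **101**.
- Upper limit only: n = (1.645 + 1.282)² V/d² = 8.564 × 0.41/0.0441 = 79.6, giving **80**.

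**3. What does give 37.** With d = 0.35, the equivalence formula gives 10.82 × 0.41/0.1225 = 36.2, rounded up to **37**. A limit of 0.35 per week means 0.6 versus 0.95, an increase of 0.35/0.6 = 58%.

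The following alternatives with the stated limit, and one on the log scale, do not return 37:

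| Variant | Equivalence | Upper limit only |
|---|---|---|
| 0.41 misread as an SD, d = 0.21 | 42 | 33 (35 with a t-test) |
| Limit ln(1.35), variance 0.41 | 50 | 39 |

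To need only 37 at d = 0.21, the variance would have to be 0.15 (equivalence) or 0.19 (upper limit only). Solving the step 1 formula for the correlation gives about 0.95 or 0.90, against the stated 0.6.

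**4. Power at the stated limit.** Upper-limit power is Φ(d/√(V/n) − 1.645). Equivalence power is twice that minus 1, or zero if negative. At n = 40, √(0.41/40) = 0.1012 and 0.21/0.1012 − 1.645 = 0.429, so upper-limit power is 0.666 and equivalence power is 0.332.

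| n | Equivalence | Upper limit only |
|---|---|---|
| 37 | 27% | 64% |
| 40 | 33% | 67% |
| 80 | 80% | 90% |
| 101 | 90% | 95% |

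**5. The limit that 40 patients support with 90% power.** Equivalence: 3.290 × 0.1012 = 0.333 per week, or 56% of 0.6. Upper limit only: 2.926 × 0.1012 = 0.296 per week, or 49%.

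**6. The 57% figure.** An equivalence test within one type (n = 20) with limit 0.35 has power 2Φ(0.35/√(0.41/20) − 1.645) − 1 = 57.6%. With limit 0.21 the equivalence power is 0, and the upper-limit power is 43%. For an actual comparison of 20 with 20, *assuming* variance 0.41 within each type, the standard error is √(2 × 0.41/20) = 0.2025. A difference of 0.21 then has 18% power two-sided or 27% one-sided. A difference of 0.35 has 41% or 53%.

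**The case against.** Four objections deserve an answer.

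*The 0.35 entry is not documented.* This is correct. A reader might infer from the exact match that the calculation used 0.35, but the protocol does not say what was entered in the software. The match makes it the best explanation and no more. The mismatch between the stated inputs and N = 37 does not depend on it.

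*The 57% proves nothing.* This is largely correct. A reader might infer that it is the power of an equivalence test within one diabetes type at limit 0.35. But 57.6% matches 57% only by truncation, and the sentence describes a between-type comparison. With 20 per type and variance 0.41, 57% would also arise for a between-type difference of about 0.43 (two-sided) or 0.37 (one-sided). The figure is roughly consistent with the same entry, but it cannot be checked without its effect size and test.

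*Using an equivalence test for an upper-sided hypothesis is not an error.* This stands. Testing each limit at one-sided 0.05 is legitimate, and it is conservative for a claim about the upper limit alone. The choice changes the power a great deal, however, so the protocol should say which test it means.

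*This is a pilot and the inputs are rough.* The inputs come from investigator consensus, and baseline may last 4 to 16 weeks, so the 3:1 ratio is only nominal. Ratios of 1.5:1 (24/16) and 6:1 (24/4) give variances of 0.44 and 0.43 by the step 1 formula, and upper-limit power of 64% to 65% at N = 40, so the shortfall remains. The protocol's caveats about limited power concern efficacy and subgroups, not this calculation. It is true that the DSMB's trigger, a lower confidence limit above 35%, works on observed data and does not depend on N = 37.

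**Conclusion.** The point holds. N = 37 does not follow from the stated inputs. The named method gives 101, and a test of the upper limit alone gives 80. Under the protocol's assumptions (variance 0.41, no true change, limit 0.21 per week), 40 patients give 33% power by equivalence or 67% for the upper limit only. A neutral treatment would therefore fail to exclude a 35% increase in about two thirds or one third of such trials, against the 10% that a power of 0.9 implies. The increase from 37 to 40 does not close the gap.

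Two further readings are tempting but not supported. A reader might take this as the only hypothesis with a stated power, but section 8.3 also claims more than 99% for the GCSI reduction. What is particular to this hypothesis is that it sets the sample size. A reader might also conclude that the trial must enrol 80 or 101 patients. For an uncontrolled pilot, 40 can stand if the protocol states honestly what 40 can show.

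**What to change.** Keep N = 40. In the synopsis and section 8.3, replace the N = 37 and 90% power claim with wording such as:

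> Under the stated assumptions, N = 40 gives 33% power by the two-sided equivalence test (67% if only the upper limit is tested, one-sided 0.05) to exclude a 35% increase (0.21 per week). Power of 90% is reached for a limit of about 0.33 per week (56%) by equivalence, or 0.30 per week (49%) one-sided.

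State which test will be used. The upper-limit test matches the hypothesis as worded, but the choice is the sponsor's. Give the variance of 0.41 in section 8.3 as well as in the synopsis.

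Recompute the 57% figure with its test and between-type difference stated, or remove it. The 18% and 27% in the working illustrate one assumed difference and are not proposed as protocol text, because the protocol names no between-type difference of interest.

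The cost is a wording change in two places and a less favourable power statement. No patients, visits or procedures are added.

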#### **8.4 Interim analysis**

An independent Data and Safety Monitoring Board (DSMB), appointed by the NIDDK, is responsible for providing input to the NIDDK regarding approval of the protocol for the GLUMIT-DG study and for monitoring the accumulated interim data as the study progresses to assess patient safety and data quality and to review efficacy. The DSMB is a multi-disciplinary group with a written charge provided by the NIDDK. The DSMB serves in a consultative capacity to the NIDDK, which will communicate with the investigators regarding the DSMB deliberations.

The DSMB meets to provide input to the NIDDK regarding approval of the protocol and supporting documents. After the study commences, the DSMB meets twice a year to review safety data and other performance issues. The DSMB may request more frequent meetings if necessary to fulfill its charge or at the discretion of the NIDDK Program Official. It may also request additional safety reports on a more frequent basis. For example, all serious adverse events are reported to the DSMB quarterly for their consideration and recommendations as they occur. The DSMB Charter provides more specific information and defines the roles, responsibilities, and activities of the DSMB.

The DSMB will review safety data when ten patients (N=10) have completed the study. The DSMB will advise on whether or not it is safe to proceed towards the full sample size of 40 patients.

No formal stopping guidelines are proposed for this pilot study of safety. However, each DSMB periodic monitoring report will include an analysis of the primary safety outcome that calculates, based on the available data, the lower 95% confidence limit on the estimated percent increase from baseline in mean weekly mild to moderate or severe hypoglycemic events during the on-treatment period. If the lower confidence limit is greater than 35%, the DSMB will be asked to discuss and vote on whether the study should continue, based on a review of all information available at that time.

---

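### The stated 90% power for the 35% limit does not hold at N=37 or N=40: N=37 does not follow from 0.6 vs 0.81, and a limit set as a percent of an estimated baseline costs further power

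*Protocol*

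**What the plan says.** The hypothesis in Protocol section 8.3 is relative: compared with each patient's baseline period, the mean weekly number of hypoglycaemic events should rise by no more than 35% on pump and RT-CGM.

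The planning step is absolute. Section 8.3 gives an "equivalence limit of 35% (0.6 vs. 0.81 episodes per week", and the design synopsis repeats it as "35% (0.6 vs. 0.81 episodes per week". The test is a one-sample equivalence z-test, "assuming one-sided Type I error of 0.05, power =0.9", with an expected increase of 0%. The synopsis words the error rate as "Type I error: 0.05 (1-sided for equivalence".

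The inputs come from investigator consensus. They are a mean of 0.6 episodes a week, an SD of 0.8 and, to link the two periods, this entry: "Assumed intra-class correlation between baseline and on-treatment weekly mild, moderate and severe hypoglycemic episodes by meter glucose: 0.6".

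The synopsis adds a variance of change of 0.41, allowing for a 3:1 ratio of on-treatment to baseline period lengths. The result is N=37, raised by about 10% to 40 to allow for departures from assumptions. For DSMB reports, section 8.4 uses "the lower 95% confidence limit on the estimated percent increase from baseline".

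**The concern.** Two things do not fit together.

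- **The number.** The stated variance, limit, error rate and power should return 37, and they do not.
- **The scale.** A limit of 35% over baseline moves with the baseline mean, and that mean is estimated in the same 40 patients. The calculation instead holds the limit at 0.21. Baseline sampling error is inside the 0.41 variance of the change, but it is absent from the limit.

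This is the primary safety hypothesis, and section 8.3 says the findings will inform whether a large randomised trial should be done. A reader who believes the 90% would take a failure to exclude a 35% increase as evidence against safety, when at the real power that result is likely even if nothing has changed.

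**Working it through.** **Inputs** (synopsis and section 8.3): SD 0.8, so variance 0.64; correlation 0.6; period ratio 3:1; mean 0.6; limit 0.35 × 0.6 = 0.21; one-sided α 0.05 (z = 1.645); power 0.90 (z = 1.282); true increase 0%. B and T are a patient's baseline and on-treatment weekly rates.

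**1. The variance reproduces.** With Var(B) = 0.64, Var(T) = 0.64/3 = 0.213 and Cov = 0.6 × √(0.64 × 0.213) = 0.222:

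Var(T − B) = 0.64 + 0.213 − 2 × 0.222 = 0.410, the plan's 0.41.

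**2. The sample size does not.**
- One-sided: (1.645 + 1.282)² × 0.41 / 0.21² = 79.6, so 80.
- Equivalence in its standard form, with β split over two sides: (1.645 + 1.645)² × 0.41 / 0.21² = 100.6, so 101.
- Two-sided α: 98 or 121. Reading 0.41 as an SD: 33 or 42.
- Equivalence with a limit of 0.35 episodes per week: (1.645 + 1.645)² × 0.41 / 0.35² = 36.2, so **37**.

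Only the last gives 37 among the combinations tried. A limit of 0.35 means 0.6 vs 0.95, and 0.35/0.6 = 58%.

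**3. Power against a fixed +0.21.** One-sided power is Φ(0.21/√(0.41/N) − 1.645). Equivalence power is twice that minus 1.

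| N | One-sided | Equivalence |
|---|---|---|
| 37 | 64% | 27% |
| 40 | 67% | 33% |
| 80 | 90% | 80% |

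**4. Power on the percent scale.** An increase below 35% means that the mean of T − 1.35B is below zero. With no true increase that mean is 0.6 − 0.81 = −0.21, as before, but the variance is larger:

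Var(T − 1.35B) = 0.213 + 1.35² × 0.64 − 2 × 1.35 × 0.222 = 0.781.

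One-sided power is Φ(0.21/√(0.781/N) − 1.645): 42% at N=37, 44% at N=40 and 68% at N=80. Simulation of normal data gave 42% and 44% at N=37 and 40. For 90% power, N is about 152.

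**5. Other variance splits at N=40.** The documents do not give the two variances separately, so the split is an assumption.

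| Split | Var(T − B) | Var(T − 1.35B) | Power, percent scale |
|---|---|---|---|
| 0.64 and 0.213, correlation 0.6 | 0.41 | 0.781 | 44% |
| 0.64 in both, correlation 0.6 | 0.512 | 0.770 | 45% |
| 0.64 in both, change variance held at 0.41 (correlation 0.68) | 0.41 | 0.632 | 51% |

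Only the first split honours the SD, the correlation and 0.41 together.

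**The case against.** Converting a relative limit to an absolute one at the planning mean is ordinary practice, and the protocol shows the conversion openly. The final test may be fixed in an analysis plan that is not at hand, and a test against +0.21 would avoid the second loss entirely. That stands, and it is why the second loss is conditional on the scale. It does not rescue the 90%, which fails against a fixed +0.21 as well. Nor do the three patients added to 37 close a gap to 80 or more.

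Four stronger readings are tempting and are not supported:

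- **That the uncertain baseline explains the whole shortfall.** It does not. At N=40, power is already 67% with the limit fixed; the percent scale removes about 22 points more. Setting 152 against 37 mixes the two causes.
- **That the plan treats the baseline as known.** Its sampling error is in the 0.41. Only the limit is fixed.
- **That the false-safe rate rises to about 12%.** Simulation gives this if the change is compared with 35% of the observed baseline as though that were a constant. The protocol does not say this will be done.
- **That the trigger in section 8.4 is wrong.** It prompts a DSMB discussion, carries no stated power, and can use a confidence limit that includes baseline uncertainty.

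The percent-scale power also depends on the method. A delta-method log-ratio test gives Φ(ln 1.35/√(0.41/(0.36 × 40)) − 1.645), about 55%. Its simulated size was about 7.7%, so part of that gain comes from a test that is too liberal.

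**Conclusion.** The stated 90% power is wrong on either scale. The main cause is that N=37 does not follow from 0.6 vs 0.81 with variance 0.41. That 0.35 was entered where 0.21 was meant is an inference from the exact match, not something the documents state. The second cause is the mismatch between a relative hypothesis and a fixed limit. It lowers one-sided power at N=40 from about 67% to about 44% (44-51% over the splits examined). Correcting the margin alone would not cure it: 80 patients give 90% against a fixed +0.21 but about 68% on the percent scale.

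These figures rest on the plan's own SD, correlation and 3:1 ratio, on a normal approximation, and on no true increase. The percent-scale figures also rest on the assumed variance split and on T − 1.35B as the test.

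**What to change.** In the synopsis and section 8.3, state whether the primary safety test is against an absolute +0.21 episodes per week or a 35% relative increase. If relative, name a method that carries the baseline's uncertainty, such as T − 1.35B or a rate ratio.

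Replace 90% with the power at N=40 for the choice made:
- **Absolute:** about 67% one-sided, or 33% if the two-sided equivalence test is kept.
- **Relative:** about 44-51% one-sided for T − 1.35B. A rate-ratio model needs its own calculation.

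Correct or withdraw the statement that N=37 follows from these inputs. The trigger in section 8.4 may stay on the percent scale, provided that its confidence limit includes the uncertainty of the baseline mean.

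The cost is a change of wording and a less favourable stated power. No added patients are needed for a pilot that reports its precision honestly.

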### 4.2 Inclusion criteria

Patients with mild to moderate symptoms of diabetic gastroparesis will be studied. Patients should not have idiopathic or post-surgical gastroparesis etiologies and must satisfy the following inclusion criteria:

1. Age 18 – 70 years old at registration
2. Type 1 or type 2 diabetes mellitus for at least 2 years
3. Symptoms of gastroparesis (nausea, vomiting, early satiety, bloating fullness, discomfort) for at least 1 year prior to registration with a Gastroparesis Cardinal Symptom Index (GCSI) score of  $\geq 18$
4. Delayed gastric emptying on gastric emptying scintigraphy within 1 year of registration, defined as greater than 60% retention at 2 hours or greater than 10% retention at 4 hours
5. Hemoglobin A1c of at least 8.0% at registration with current therapy (insulin and/or oral hypoglycemic agents). This level of HbA1c indicates the need to advance treatment and makes the patient a candidate for insulin treatment (for those using oral agents only) or optimization of insulin therapy. Individuals already receiving diabetes therapy via an insulin pump will be eligible for participation if, in the opinion of investigators, he/she may acquire additional benefit from RT-CGM that might improve glycemic control
6. Normal upper endoscopy within 1 year of registration
7. No clinical or imaging evidence of obstruction
8. Successful use of the RT-CGM during the screening period
9. Access to a computer running Windows and with internet capabilities

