#### **Patient Assessment of Upper Gastrointestinal Disorders - Symptom Severity Index (PAGI-SYM).**

A validated 20 question questionnaire that measures symptoms of gastroparesis, dyspepsia, and gastroesophageal reflux disease on a 0 to 5 scale for each symptom^18.

**Patient Assessment of Upper Gastrointestinal Disorders - Quality of Life (PAGI-QOL).** A validated 30 question questionnaire that measures quality of life in upper gastrointestinal disorders.

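### The GCSI power statement in section 8.3 uses a baseline of 27 ± 15 that does not fit the entry floor of 18, and its single figure of >99% is not supported

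*Protocol*

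**What the plan says.** Section 8.3 (Statistical issues) gives one quantified power statement for symptoms. It starts from "A 25% reduction in mean from a baseline GCSI score of" 27 ± 15 and assumes that this falls to 20 ± 15. The power claim attached to that fall reads: "with a sample size of 40, can be detected with >99% power, again assuming a Type I error of 0.05 and a modest intra-class". The last, cut-off term refers to how strongly the two GCSI scores of a patient are correlated. The section gives no number for that correlation, no sidedness for this test and no source for the means and SDs.

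Section 4.2 (Inclusion criteria), criterion 3, requires symptoms "for at least 1 year prior to registration with a Gastroparesis Cardinal Symptom Index (GCSI) score of" 18 or more. The synopsis repeats this. Section 4.2 also says "Patients with mild to moderate symptoms of diabetic gastroparesis will be studied".

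Section 5.8 describes the 20-item PAGI-SYM as scored "on a 0 to 5 scale for each symptom". Neither the number of GCSI items nor the maximum GCSI score appears in the protocol.

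Two nearby figures belong to the primary hypoglycemia outcome and are not restated for the GCSI: "assuming one-sided Type I error of 0.05, power =0.9", and "Assumed intra-class correlation between baseline and on-treatment weekly mild, moderate and severe hypoglycemic episodes by meter glucose: 0.6".

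**The concern.** The planned comparison concerns the enrolled patients, and every one of them scores at least 18 when admitted. A baseline SD of 15 around a mean of 27 puts the floor only 0.6 SD below the mean, so the planning distribution includes many patients whom the trial would turn away.

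The floor acts on the baseline score and not on follow-up. Equal SDs at the two times are therefore unlikely, and the SD of the change, which sets the power of a before-after comparison, is not the one planned. This sentence is the only numerical support for the claim in section 8.3 that 40 patients give adequate power for some symptom measures.

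**Working it through.** **Inputs.** From section 8.3: baseline mean 27, follow-up mean 20 (a fall of 7; exactly 25% of 27 is 6.75), SD 15 at both times, N = 40, Type I error 0.05. From section 4.2: floor 18. Assumed here: a paired t-test, and correlations r from 0.2 to 0.6, because the protocol gives none for the GCSI. The upper end is the value it uses for hypoglycemia.

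**1. The plan's own figure.** SD of change = √(s₁² + s₂² − 2·r·s₁·s₂). With 15/15 and r = 0.6 this is √(450 − 270) = 13.4. The noncentrality is 7·√40/13.4 = 3.30, and two-sided power is 90% (one-sided 94%). At r = 0.3, 0.4 and 0.5 it is 68%, 75% and 82% two-sided (79%, 84% and 90% one-sided). The >99% is therefore not reproduced at any correlation usually called modest.

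For 99% power the SD of change must be at most 10.07 two-sided or 10.95 one-sided. Since r = 1 − SD²/450, that means r of 0.78 or 0.73. With a fall of 6.75 it is 0.79 or 0.75. By the normal approximation the values are 0.76 and 0.72 for a fall of 7, and 0.78 and 0.74 for 6.75. About 0.74 one-sided and 0.78 two-sided summarises these.

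**2. Share below the floor.** Φ((18 − 27)/15) = Φ(−0.6) = 0.274, and 0.274 × 40 ≈ 11 patients, if scores are roughly normal.

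**3. Largest possible SD.** On a scale from 18 to M with mean 27, the SD is largest when every patient sits at one end or the other: √((27 − 18)(M − 27)).

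| Scale maximum M (not stated) | Largest SD |
|---|---|
| 45 | 12.7 |
| 50 | 14.4 |
| 52 | 15.0 |

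At M = 52, SD 15 requires 9/34 = 26% of patients at 52 and 74% at exactly 18.

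**4. Floor-compatible SDs.** Three illustrative shapes with floor 18 and mean 27:
- uniform on 18 to 36: 18/√12 = 5.2
- 18 plus a gamma of shape 2: 9/√2 = 6.4
- 18 plus an exponential: 9.0

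If 27/15 instead described a normal group before the floor is applied, those at 18 or above would have mean 33.9 and SD 10.8 (30.4 and 7.3 if also capped at 45). The mean would then be off as well.

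**5. Power for a 7-point fall** (noncentral t, two-sided 0.05, N = 40):

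| Baseline SD | Follow-up SD | r = 0.2 | r = 0.4 | r = 0.6 |
|---|---|---|---|---|
| 15 | 15 | 62% | 75% | 90% |
| 9 | 15 | 78% | 87% | 95% |
| 5 | 15 | 83% | 88% | 93% |
| 9 | 10 | 95% | 98.5% | 99.9% |
| 5 | 10 | 98.8% | 99.7% | >99.9% |

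Example: for 9/15 at r = 0.2, the SD of change is √(81 + 225 − 54) = 15.9, and power is 78%.

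**6. Direction of the effect.** With the follow-up SD held at s₂, lowering the baseline SD from s₂ to s₁ reduces the SD of change whenever r < (s₁ + s₂)/(2·s₂). With s₂ = 15 that is r < 0.67 for s₁ = 5 and r < 0.80 for s₁ = 9. It holds over the whole range in the table.

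**The case against.** The strongest reply is that the misfit works in the protocol's favour. At each correlation from 0.2 to 0.6, a floor-compatible baseline SD gives more power than 15/15, so 15 is a conservative input. This stands. A reader might infer that the entry floor is what brings power down to 78%. It is not: that low end comes from a low correlation combined with keeping the protocol's follow-up SD of 15. Selection at the floor also weakens the correlation. In a simulated case, 0.60 becomes about 0.34 after truncation to 18 to 45. Even so, the SD of change falls from 13.4 to about 12.4, and two-sided power is about 95% against 90% to 91% for 15/15.

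A reader might also conclude that 27 ± 15 is impossible. That is strict only if the scale maximum is below 52, and the protocol gives none; the 27% figure likewise assumes normality. Nor does the protocol show that the figures come from an unselected population. It names no source, and its reference to the investigators' consensus concerns the hypoglycemia estimates.

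A more efficient analysis would help. At r = 0.6, one-sided and by normal approximation, adjusting for baseline gives 98.0% and averaging the two follow-up visits gives 98.5%. Neither exceeds 99%, and neither is stated.

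Finally, the stakes are low. The sample size came from the primary safety outcome (37, raised to 40), and section 8.3 says that a larger controlled study would be needed for evidence of efficacy. That limits the severity but does not make the sentence correct.

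**Conclusion.** The point holds, as a minor one. The baseline input of 27 ± 15 does not fit the protocol's own entry rule. It would place about 27% of a normal population below the floor, and it is attainable only on a scale reaching at least 52, with scores piled at the two extremes if the maximum is exactly 52. Such a split sits badly with a group described as having mild to moderate symptoms. Implausible is the supportable word; impossible would need a stated maximum below 52.

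Separately, the single figure of >99% is not supported. On the protocol's own SDs it needs a correlation of about 0.74 to 0.78. On floor-compatible baseline SDs of 5 to 9, two-sided power is about 95% to >99% if the follow-up SD is 10 or less, and about 78% to 95% if it is 15. These ranges rest on a paired t-test, a 7-point fall, correlations of 0.2 to 0.6 and illustrative baseline shapes. They do not overturn the broader claim of reasonable power for some symptom measures. Neither the primary outcome nor the sample size is touched.

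**What to change.** In section 8.3:
- Replace 27 ± 15 with a mean and SD for diabetic patients scoring 18 or more, and give the source. The Gastroparesis Registry, named as a recruitment source in sections 3.1 and 5.2, could supply them if it holds such scores, which the protocol does not say. Otherwise label the values as assumptions.
- State the range of the GCSI score.
- Allow the baseline and follow-up SDs to differ, and base the calculation on the SD of the change.
- Give the correlation as a number and state whether the test is one- or two-sided.
- Replace >99% with a range of power over the stated inputs.

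The cost is a rewritten sentence and, if the data exist, one tabulation. Sample size and design stay as they are.
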